## Background

Cerebellar disease results in well-known motor performance deficits, including ataxia of stance and gait, limb incoordination, dysarthria, and oculomotor abnormalities. During the last decades, there has been growing evidence that cerebellar disease is not only accompanied by motor disturbances but also by cognitive and affective symptoms (see [1–3] for reviews). As early as 1998, Schmahmann and Sherman introduced the *Cerebellar Cognitive Affective/ Schmahmann Syndrome (CCAS)* [4]*.* The core symptoms of CCAS are difficulties with executive, linguistic and visuospatial functions as well as problems with the regulation of emotion and affect. Since its original description, evidence for the presence of CCAS has been accumulating in pediatric and adult patients suffering from different cerebellar diseases including various hereditary ataxias, cerebellar tumors, and cerebellar stroke [1–3]. In recent years, advances in structural and functional brain imaging allowed for detailed mapping of cognitive functions in the posterolateral cerebellar hemisphere [5–9]. As yet, diagnosis of CCAS relies on non-standardized bedside cognitive examination and, if available, detailed neuropsychological test batteries. Until recently, there has not been a validated bedside test that was able to reliably screen for CCAS in cerebellar patients – unlike well-established bedside tests for dementias or mild cognitive impairment (MCI), i.e. Mini Mental State Examination (MMSE) or Montreal Cognitive Assessment (MoCA). However, MMSE and MoCA are of limited use to screen for CCAS because cerebellar patients frequently perform within the normal range [10]. Recently, Schmahmann and colleagues [10] have developed a bedside test designed to screen for CCAS in adults. In order to develop this CCAS Scale, they first applied a broad battery of 36 well-established neuropsychological tests in a large group of cerebellar patients primarily suffering from cerebellar degeneration. In the novel CCAS Scale, tests were implemented which captured the core cognitive domains of CCAS, distinguished best between cerebellar patients and controls, and at the same time were short and easy enough to be applied in a bedside setting. These include test items for semantic and phonemic fluency, category switching, verbal registration and delayed verbal recall, digit span forward and backward, cube draw and copy, similarities, go/ no-go, and affect. Single tests can either be passed reaching a specific cut-off score or failed. CCAS is considered possible if one test is failed, probable if two tests are failed, and definite if three or more tests are failed. Version A of the CCAS Scale has then been validated in another US-American cohort of 39 adult cerebellar patients, including patients with cerebellar degeneration and focal cerebellar lesions and 55 matched healthy controls. It exhibited high values for selectivity [that is the ability to distinguish between patients and controls, or in other words preventing controls from being diagnosed as patients; possible/ probable/ definite CCAS: 78/ 93/ 100%] and reasonable sensitivity [that is the probability that a patient is identified as a patient; possible/ probable/ definite CCAS: 95/ 82/ 46%]. Furthermore, it showed modest internal consistency using Cronbach’s alpha value (= 0.59) indicating that no test item within the scale measures the exact same domain(s) as another item. Thus, no test item is redundant. Comparing patients with pure cerebellar lesions and patients with additional extracerebellar involvement the authors found that difficulties in verbal registration and delayed verbal recall were more prominent in the latter. Therefore, poor performance in these two test items is indicative of extracerebellar involvement (“red flag”). In addition to the pass/ fail criteria which are used to screen for CCAS, a total sum score is calculated which allows for follow-up examinations in individual patients [10]. Three parallel versions B-D were developed to enable repeated assessments. In the present study preliminary German versions of the CCAS Scale are introduced, and the study protocol for their validation is presented.

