
## Methods

### Study aims

The first primary aim of this study was to create preliminary German versions of the CCAS Scale. The second primary aim will be their validation in a large cohort of patients with various cerebellar disorders and healthy age-, sex-, and education-matched controls. Secondary aims will be to examine possible relationships between clinical features such as disease duration or severity of cerebellar motor symptoms, and the CCAS score.

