##### Study sample

For validation of version A at least 65 patients and an equal number of matched healthy controls will be recruited. About one third (≥ 25) of the patients will suffer from disorders that primarily affect the cerebellum (isolated cerebellar disease = cer-pure: 1. degenerative cerebellar disorders, e.g. spinocerebellar ataxia type 6 (SCA6); 2. focal cerebellar lesions, e.g. cerebellar stroke). The other two thirds (≥ 40 patients) will suffer from disorders with additional extracerebellar involvement (cerebellar plus disease = cer-plus: 1. degenerative cerebellar disorders, e.g. SCA1, 2 or 3; 2. focal cerebellar lesions, e.g. cerebellar stroke with additional involvement of the brain stem). Group assignment in patients with cerebellar degeneration goes by diagnosis: A genetic disease, which is known to involve extracerebellar regions, is considered a “cer-plus form”, although the clinical phenotype at the time of testing may be pure cerebellar.

An equivalent number of healthy matched participants will serve as controls. Each patient will be matched with a control participant of same sex, similar age (interval: +/− 5 years) and similar years of education (intervals: < 9 yrs., 9–10 yrs., 11–13 yrs., 14–16 yrs., > 16 yrs.). We will use the same matching criteria as in [10] except for education matching because of the different educational systems in Germany and the United States.

Parallel versions B-D will be validated in groups of 25 patients (cer-pure and cer-plus, respectively) and 25 matched healthy controls each.

Patients in this investigator-initiated, multicenter study will be recruited from the ataxia clinics at the Departments of Neurology of the University Hospitals in Aachen, Bonn, Duesseldorf, Essen, Heidelberg and Tuebingen, as well as from the MediClin Fachklinik Rhein-Ruhr in Essen, and the Departments of Neurosurgery of the University Hospital in Essen and at the Klinikum Dortmund. Essen is the coordinating site. Furthermore, we will collaborate with the “Deutsche Heredo-Ataxie Gesellschaft e.V. (DHAG)”, a patient support group, and patients will be recruited via their newsletter and webpage. Healthy controls will be recruited from patients’ families and by public bulletins.

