##### Demographics and clinical assessment of cerebellar motor syndrome

Demographics including years of education and employment, educational achievements as well as occupational and marital status will be recorded. For patients, medical records and available brain scans will be evaluated. Age of onset, disease duration and in case of genetically proven nucleotide repeat diseases the repeat length will be documented. Furthermore, a detailed medical history will be taken, and a neurological examination will be performed in every participant. Severity of cerebellar ataxia in patients will be evaluated using different clinical ataxia scales: The Scale for the Assessment and Rating of Ataxia (SARA) [13] will be used because of its widespread use. In addition, the International Cooperative Ataxia Rating Scale (ICARS) [14] will be used because it includes rating of cerebellar oculomotor deficits. Its short form – BARS – [15] will be used to enable direct comparison with the original US-American validation study. The SpinoCerebellar Ataxia Functional Index (SCAFI) [16] will be assessed because it allows for a more objective quantification of motor deficits. Finally, non-ataxia signs will be assessed semi-quantitatively using the Inventory of Non-Ataxia Signs (INAS) [17].

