##### Data analysis

Selectivity and sensitivity will be assessed using the same cut-off values for individual test items, and the same three pass/ fail criteria determined in the original study by Hoche et al. [10] (that is: possible CCAS = one test failed; probable CCAS = two tests failed; definite CCAS = three or more tests failed). To assess selectivity the percentage of true negatives will be calculated, that is the percentage of controls which have been correctly identified as controls [number of controls identified as controls/ true number of controls in the sample * 100]. To assess sensitivity the percentage of true positives will be calculated, that is the percentage of patients which have been correctly identified as patients [number of patients identified as patients/ true number of patients in the sample * 100]. In case selectivity and sensitivity falls below the values of the original CCAS Scale, selectivity and sensitivity of individual tests will be assessed. Cut-off values of single test items and/ or cut-offs defining (possible/ probable/ definite) CCAS will be adjusted to achieve high selectivity and reasonable sensitivity – comparable to the values of the original CCAS Scale.

Differences between patient groups (pure cerebellar disease vs. patients with additional extracerebellar involvement) will also be analyzed. We want to verify that difficulties in verbal registration and delayed verbal recall are indicative of extracerebellar involvement (“red flags”). In further accordance with Hoche et al. [10], Cronbach’s alpha will be used to assess the inter-relatedness of the individual test items, i.e. internal consistency.

To study construct validity of the CCAS Scale subtests of validated German versions of neuropsychological test batteries will be used as the external criterion. We will compare the percentage of patients diagnosed with CCAS based on a detailed neuropsychological test battery with the percentage of patients identified by the CCAS Scale.

Finally, correlations between age, disease duration, severity of cerebellar motor symptoms (measured by clinical ataxia scores), and total CCAS sum score will be calculated. All raw data (thus total number of failed tests respective total sum score and sub scores on single test items) will be tested for normal distribution using Kolmogorov-Smirnov tests. Parametric or non-parametric tests will be applied depending on distribution and final sample size.

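### The planned correlations of ataxia scores and disease duration with the CCAS sum score take no account of the cer-pure/cer-plus grouping; an estimate adjusted for group would be safer at almost no cost (low severity)

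*Protocol article*

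**What the plan says.** Under Study aims, the article states: "Secondary aims will be to examine possible relationships between clinical features such as disease duration or severity of cerebellar motor symptoms, and the CCAS score". Data analysis answers this with a single sentence: "correlations between age, disease duration, severity of cerebellar motor symptoms (measured by clinical ataxia scores), and total CCAS sum score will be calculated". The sentence mentions neither patient group nor any covariate. The choice between parametric and non-parametric tests is left to the distribution and the final sample size.

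Study sample fixes who enters these correlations. "For validation of version A at least 65 patients and an equal number of matched healthy controls will be recruited". Of the patients, "About one third (≥ 25) of the patients will suffer from disorders that primarily affect the cerebellum", and "The other two thirds (≥ 40 patients) will suffer from disorders with additional extracerebellar involvement".

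Two other places treat this grouping as relevant to cognition. Background reports from the original American validation, comparing pure cerebellar with additional extracerebellar disease, that "difficulties in verbal registration and delayed verbal recall were more prominent in the latter". Data analysis plans to compare the two groups and to confirm this pattern in the German cohort. The section on demographics and clinical assessment adds that non-ataxia signs are scored with the INAS. Neither the group nor the INAS is given a role in the correlations.

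**The concern.** Verbal registration and delayed recall are items of the scale, so the article's own expectation implies some cer-pure/cer-plus difference in the sum score. If the groups also differ in ataxia score or disease duration, mixing them induces a correlation even when there is none inside either group. A reader of the results could then take a difference between disease groups for a relation between motor severity and cognition.

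What is at stake is the interpretation of a descriptive secondary result. The grouping that could distort it is one that the study itself defines, recruits on and records.

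**Working it through.** **Inputs from the article.** n₁ = 25 cer-pure and n₂ = 40 cer-plus (Study sample). Their sum, 25 + 40 = 65, reproduces the stated minimum. The shares are 25/65 = 38.5% and 40/65 = 61.5%. The article gives no alpha, power or effect size for the 65, and no group difference in ataxia or sum score.

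**Assumptions.** Two-sided 5% test; normal scores with equal variance within groups; zero correlation within each group; group differences d_x (ataxia score) and d_y (sum score) in within-group SDs, with cer-plus worse on both. The range of d is assumed.

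**Step 1: induced correlation.** With p = 25/65, p(1−p) = 1000/4225 = 0.2367, and

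|r| = 0.2367·d_x·d_y / √[(1 + 0.2367·d_x²)(1 + 0.2367·d_y²)].

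For d_x = d_y = d this reduces to 0.2367d² / (1 + 0.2367d²). At d = 1.0, for example, 0.2367/1.2367 = 0.19.

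**Step 2: how often it is significant.** The critical |r| at n = 65 is 0.244. Rates are from 20,000 simulated studies per setting, using Pearson correlations.

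| d_x, d_y (SD) | induced \|r\| | significant, pooled | significant, adjusted for group |
|---|---|---|---|
| 0.2, 0.2 | 0.01 | 5.3% | 5.1% |
| 0.5, 0.5 | 0.06 | 7.3% | 5.1% |
| 0.8, 0.8 | 0.13 | 18.3% | 5.0% |
| 1.0, 1.0 | 0.19 | 33.9% | 5.0% |
| 1.2, 1.2 | 0.25 | 55.6% | 5.3% |
| 0.2, 0.8 | 0.04 | 6.0% | 5.3% |
| 0.5, 1.0 | 0.10 | 12.8% | 5.2% |
| 0, 0.8 | 0 | 5.1% | 4.9% |

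The induced r reaches the critical value of 0.244 only when d = √[0.244 / (0.756 × 0.2367)] ≈ 1.17 SD on both scores.

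**Step 3: price of the remedy.** Power by Fisher's z is Φ(atanh(r)·√(n−3) − 1.96). Adjusting for one binary covariate replaces n−3 = 62 by 61.

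- True r = 0.3: 68.3% pooled, 67.6% adjusted.
- True r = 0.4: 91.6% pooled, 91.1% adjusted.
- Fully separate analyses at r = 0.4: 51% in 25 cer-pure patients (n−3 = 22) and 73% in 40 cer-plus patients (n−3 = 37).

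Adjustment is therefore nearly free, while splitting the sample as the main analysis is not.

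**The case against.** The best case against the point has four parts.

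*Silence is not pooling.* The sentence does not say that the groups are combined, and a journal article condenses a fuller plan in which an exploratory correlation might be stratified. This is fair as far as it goes. But the article does name the cer-pure/cer-plus split for another analysis in the same section and does not carry it over. Taken as written, the sentence describes plain correlations. If the full plan already adjusts, one clause settles the matter.

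*The aim makes no causal claim.* A reader might infer that the study attributes poorer cognition to cerebellar motor severity. The text supports only an examination of possible relationships, and a cohort-wide association is a legitimate descriptive quantity. This stands and lowers the priority.

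*Half of the mechanism is undocumented.* A reader might also infer that extracerebellar disease will by itself produce the correlation. That needs a group difference on both scores. The article supports one on the cognitive side only, for two of many items, and nowhere says that cer-plus patients are more ataxic. It even notes that genetic disease counts as cer-plus by diagnosis although the phenotype at testing may be purely cerebellar, and focal lesions occur in both groups. Nothing in it supports differences of 1 SD or more on both scores. This stands: the upper rows of assumed differences show what is possible, not what is expected. Nor does the article say that the INAS is collected to separate these influences, or that opposite patterns within the groups might cancel.

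*The group comparison already covers it.* The planned comparison can show whether the groups differ on the scale. It does not remove such a difference from the correlation.

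**Conclusion.** The point holds as a low-severity improvement of the analysis. The correlations are specified without the grouping by which patients are recruited, and the article itself expects that grouping to affect part of the outcome. Whether this distorts the result depends on an unknown: the group difference in ataxia score or disease duration. With equal differences on both scores, the false-positive rate is close to nominal at 0.5 SD (about 7%), noticeable at 0.8 SD (about 18%), and large only at about 1 SD and above (34% at 1.0, 56% at 1.2). It stays near 5% if only one score differs.

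These figures rest on 25 and 40 patients, normal scores, Pearson correlations and no relation within groups. No figure in the article is wrong, and the primary aim of selectivity and sensitivity is untouched.

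**What to change.** Add a sentence to Data analysis: the overall relation of each ataxia score and of disease duration with the CCAS sum score will be estimated as a partial correlation adjusted for cer-pure/cer-plus group, or as its rank-based equivalent where non-parametric methods are chosen. The correlations within each group will be shown alongside with confidence intervals, as description only, because 25 and 40 patients give imprecise estimates.

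Two sensitivity analyses are optional: further adjustment for the INAS, since assignment by diagnosis need not match the signs present at testing, and repetition with a sum score that leaves out verbal registration and delayed recall. Neither was simulated here.

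The cost is wording only. Group and INAS are already recorded, no patients or procedures are added, and the adjusted estimate loses less than one percentage point of power at true correlations of 0.3 and 0.4.

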## Perspective

Clinical ataxia scales have been validated to rate the severity of motor symptoms in cerebellar disease [13–17], but so far there has not been a validated clinical scale to screen for the presence of the Cerebellar Cognitive Affective/ Schmahmann Syndrome (CCAS), and quantify CCAS severity. Only recently, Schmahmann and collaborators have developed and validated a promising screening tool for the CCAS – the CCAS Scale – for an American English-speaking population [10]. Till now, no validated German versions of the scale exist. German versions of the CCAS Scale are highly desirable to screen for the presence of CCAS in a clinical setting, but also for patient characterization and stratification in future therapeutical trials. The CCAS sum score may also serve as a therapeutic marker, but this would need future studies to show its sensitivity to change, and if this would be the case, its treatment responsiveness. In this multicenter study, four parallel versions (A-D) of the German CCAS Scale will be validated in a large cohort of German-speaking patients with cerebellar disorders. The parallel versions will allow multiple testing without practice effects.

The primary aim of our validation study is to show high selectivity, that is to show that the German versions of the scale are able to differentiate between patients and controls. We will test whether the pass/ fail criteria used to determine the presence of CCAS in the original scale also apply for the German scale. Cut-off values of individual test items and the pass/ fail criteria shown in Fig. 1 are taken from the US-American original and may change depending on findings in the German validation cohort. Furthermore, future studies are needed to test for possible age effects, and the need for age-dependent cut-off values and pass/ fail criteria. After full validation of the scale the implementation of a web-based training tool is planned.

We are interested whether the scale is able to screen for CCAS in patients with degenerative diseases, but also suffering from cerebellar stroke or surgical lesions due to cerebellar tumors. In the validation study of the original American English CCAS Scale only few patients with focal cerebellar lesions were tested [10]. In part of the patients with focal lesions brain MRI scans will be available. This will allow to map dysfunction in the different cognitive domains to lesions in specific cerebellar regions. For example, we expect that language dysfunction is associated with lesions of the right posterolateral cerebellar hemisphere, and visuospatial disabilities with lesions of the left posterolateral cerebellar hemisphere [6].

A limitation of the CCAS Scale is that detection of the neuropsychiatric abnormalities highly depends on the examiner’s expertise. The authors of the US-American original were aware of this weakness and gave this item (“Affect”) a weak denominator for the total sum score [10]. Additionally, administration of more detailed scales of neuropsychiatric dysfunction are recommended [24]. In future studies, expert neuropsychiatric assessments would be of interest as a further external criterion. Furthermore, testing of construct validity has some limitations. We will perform detailed neuropsychological testing only in a subset of patients. More importantly, although the core symptoms of CCAS are well described, as yet there are no standard criteria to diagnose CCAS based on detailed neuropsychological testing. Another approach to test construct validity would be to compare CCAS scores in patients with cerebellar diseases and patients with non-cerebellar neurological diseases in the future. Despite these limitations the CCAS Scale has been shown to be more sensitive to detect cognitive and affective changes in cerebellar disease than the Mini-Mental State Examination and the Montreal Cognitive Assessment [10]. The validated German CCAS Scale will allow trained healthcare personnel to screen for cognitive and affective symptoms in patients with cerebellar diseases in German-speaking countries.

## Data Availability

The datasets used to analyse the pretesting experiment are available from the corresponding author on reasonable request.

## Abbreviations

ADHD: Attention Deficit Hyperactivity Disorder
ANO10: Spinocerebellar Ataxia, Autosomal-Recessive Type 10
BARS: Brief Ataxia Rating Scale
CCAS: Cerebellar Cognitive Affective/ Schmahmann Syndrome
CNRS: Cerebellar Neuropsychiatric Rating Scale
DFG: Deutsche Forschungsgemeinschaft
D-KEFS: Delis-Kaplan Executive Function System
DRKS: Deutsches Register Klinischer Studien
EA1/2: Episodic Ataxia Type 1/2
Eng.: English
EQ-5D-3L: EuroQuol – 5 Dimension – 3 Level Questionnaire
Fig.: Figure
Ger.: German
ICARS: International Cooperative Ataxia Rating Scale
ID: Identity
INAS: Inventory of Non-Ataxia Signs
MCI: Mild cognitive impairment
MMSE: Mini-Mental State Examination
MoCA: Montreal Cognitive Assessment
MSA-C: Multisystem Atrophy Cerebellar Type
PHQ-9: Patient Health Questionnaire (Depression Part)
ROCFT: Rey–Osterrieth Complex Figure Test
SARA: Scale for the Assessment and Rating of Ataxia
SCAFI: SpinoCerebellar Ataxia Functional Index
SAOA: Sporadic Adult Onset Ataxia
SCA1/2/3/6/8/14: Spinocerebellar Ataxia Type 1/2/3/6/8/14
Tab.: Table
UMEA: University Medicine Essen Clinician Scientist Academy
US (−American): United States (American)
vs.: Versus
WAIS-IV: Wechsler Adult Intelligence Scale – 4th edition
yrs.: Years
WMS-IV: Wechsler Memory Scale – 4th edition
